**3.2.3 Withdrawal:**

- When one of the exclusion criteria develop during enrolment
- Protocol violation: failure to complete the directly observed malaria treatment
- Protocol violation: consuming less than 10 sachets of RUF in 2 weeks when in treatment arm
- Erroneous inclusion of the patient.

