# 3. STUDY DESIGN AND METHODS

**3.1 Study design**

The study design is that of a randomised intervention study. Children with confirmed *P. falciparum* malaria, meeting all study inclusion criteria, will be enrolled in the study for a period of 28 days. Participants will be assigned at random to either the intervention or the control group.

The intervention group will receive treatment for malaria plus 1 bag of RUTF per day for 14 days. The control group will receive treatment for malaria without provision of RUTF.

Random allocation to either intervention or control group is thought to be acceptable by the population as RUTF is seen as a medicine rather than a food item. A similar study did not meet a problem with randomisation.[[18]](#footnote-2) For other illnesses, the participants will be offered medical treatment according to the best local standards.

Follow-up visits will be scheduled for directly observed treatment for malaria (day 0, 1 and 2), malaria parasite density and clearance (D0, D2, and until slide is negative; and for weight measurements at day 0, 1, 13 and 27. Weight will be measured twice at each visit by two independent observers. A detailed questionnaire will be conducted at the start, and at day 13 and 27.

All participants who attend follow up sessions at the clinic will receive a small incentive[[19]](#footnote-3)* in order to compensate for lost time due to participation in the study (RUTF will not be given to the control group at the end of the study).

The study will be conducted in the period (May-June) that is likely to have a stable prevalence of malnutrition, a stable incidence of *P. falciparum* malaria and other morbidities (e.g. pneumonia and diarrhoea). The total duration of the data collection will be 2 months for data gathering: 4 weeks of enrolment (40 participants per week) and 4 weeks of follow up (the last follow-up being done 4 weeks after the last enrolment).

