**3.2.2 Exclusion criteria**

- Children who are exclusively breast fed or
- Children who are severely malnourished (MUAC <110 mm and/or bilateral oedema, or WHO weight-for-Height criteria <3 Z-scores) or
- Presence of general danger signs or signs of severe malaria as defined by the WHO criteria, or
- Known history of allergy to malaria drugs, or
- Having a sibling enrolled in the study.

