**7.4 Malaria treatment**

## In order to achieve a similar compliance with malaria treatment in the two study arms, directly observed malaria treatment will be implemented in both groups.

## Children will remain under observation for 30 minutes after treatment to ensure they don’t vomit their medication. If they do vomit the medication within 30 minutes, the same treatment regimen will be given again and children will again remain under observation for 30 minutes.

Parasite clearance will be monitored by blood slide readings on D2. Treatment failure will be assessed on D2, including parasitaemia higher than D0 count. In the case of treatment failure, a 2nd line treatment regimen will be used, as per local MSF treatment protocols. These children will be withdrawn from the study.

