| (persistent vomiting several times) | | | | | |  | No |  | |  | | |
|  | |  | |  | |  | Don’t know |  | |  | | |
|  | |  | |  | |  |  |  | |  | | |
| 8. Has your child visited a health facility since your previous visit? | | | | | | | Yes | |  | | |  |
|  | | | | | | | No | |  | | |  |
| 9. Which medication has your child taken since your previous visit? | | | | | | |  | |  | | |  |
| (other than the anti-malaria) | | | | | | | None | |  | | |  |
|  | | | | | | | Drug: | | | | |  |
|  | | | | | | |  | | | | |  |
| 10. Do you feel the child is completely recovered from the malaria episode? | | | | | | | Yes | | | | |  |
|  | | | | | | | No | | | | |  |
| If not, why do you think the child did not recover yet? | | | | | | | Don’t know | | | | |  |
|  | | | | | | |  | | | | |  |
|  | | | | | | |  | | | | |  |
|  | | | | | | |  | | | | |  |
| 11. **During the last 2 weeks** did she/he eat (food or breast milk)? | | | | | | | Much less | | | | |  |
| less then usual, about the same amount, or more than usual. | | | | | | | Somewhat less | | | | |  |
| *IF LESS, PROBE: Was he/she eating much less than usual or somewhat less* | | | | | | | About the same | | | | |  |
|  | | | | | | | More | | | | |  |
|  | | | | | | | Somewhat more | | | | |  |
|  | | | | | | | Much more | | | | |  |
|  | | | | | | | Don’t know | | | | |  |
|  | | | | | | |  | | | | |  |
|  | | | | | | |  | | | | |  |
|  | | | | | | |  | | | | |  |
|  | | | | | | |  | | | | |  |
| **ATTENTION: Question 12, 13 and 14 are only for the RUTF group on day 13** | | | | | | |  | | | | |  |
|  | | | | | | |  | | | | |  |
| 12. During the last 2 weeks how many days did your child eat 1 complete | | | | | | | ........ days | | | |  | |
| Plumpynut? | | | | | | |  | | | | |  |
|  | | | | | | |  | | | | |  |
| 13. How many plumpynut has your child eaten the last 14 days? | | | | | | |  | | | | |  |
|  | | | | | | |  | | | | |  |
| 14 How many empty sachets are returned? | | | | | | |  | | | | |  |
|  | | | | | | |  | | | | |  |

Thank you.

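### Withdrawal for eating fewer than 10 sachets applies to the RUTF arm only and breaks the randomised comparison, and the protocol does not keep withdrawn children in follow-up

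*Protocol*

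**What the plan says.** Section 3.1 sets up a randomised comparison: "Participants will be assigned at random to either the intervention or the control group". The Objective and section 2 ask what providing RUTF does for catch-up growth.

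Section 3.2.3 then withdraws children after enrolment on four grounds:
- "When one of the exclusion criteria develop during enrolment". Section 3.2.2 counts severe malnutrition and signs of severe malaria among the exclusion criteria.
- The supervised course of antimalarial drugs is not finished, in either arm.
- Low intake of the supplement: "Protocol violation: consuming less than 10 sachets of RUF in 2 weeks when in treatment arm".
- Inclusion in error.

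Section 7.4 adds malaria treatment failure, assessed on D2: "These children will be withdrawn from the study".

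Intake is recorded in Annex 4, which notes that "Question 12, 13 and 14 are only for the RUTF group on day 13". Section 3.1 schedules the two-week weight for the same visit.

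Section 3.2.4 promises active follow-up for missed appointments but does not mention withdrawn children. The data analysis part of section 10 specifies a linear regression on intervention status and names no analysis set.

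**The concern.** The sachet rule has no counterpart among controls. Appetite and intercurrent illness plausibly drive both how much RUTF a child eats and how much weight the child gains, and section 5 itself lists anorexia and incident disease among the factors that influence weight. The rule would then take poor gainers out of the RUTF arm while similar children stay among the controls. What remains compares children who ate most of their ration with controls who were never selected in that way. That is a different question from the effect of provision, and it can show a benefit where there is none.

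The other rules apply to both arms but also select on events after randomisation. A child withdrawn on D2, or when an exclusion criterion develops, may have no two-week weight. A child withdrawn for low intake may have no four-week weight, which the sustained-gain outcome needs. Withdrawal for severe malnutrition removes children because of the outcome itself, and it also touches the secondary outcome of children who lost weight.

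**Working it through.** **Inputs from the protocol (section 3.3).** Expected two-week gain is 0.09 kg (SD 0.44) in controls and 0.44 kg (SD 0.33) with RUTF, a planned difference of 0.35 kg. The test is two-sided at 5% with 80% power. The proposed size is 100 per group. The check uses 80 per arm, which is 100 less the 20% loss to follow-up that the protocol allows for.

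**The plan's own figure.** Unequal variances: n = (0.44² + 0.33²)(1.960 + 0.842)² / 0.35² = 19.4, so 20 per group, as stated. The sample size is not in question here.

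**Inputs not in the protocol (assumed).** q is the fraction of the RUTF arm below 10 sachets, and r is the correlation between intake and weight gain. Withdrawn children are taken to be left out of the analysis.

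**Sachet rule alone, no true effect.** With z_q the q-quantile of the standard normal distribution, φ its density and λ = φ(z_q)/(1 − q):
- bias b = r × 0.44 × λ
- variance factor in the RUTF arm v = 1 − r²λ(λ − z_q)
- SE = 0.44 × √(v/(80(1 − q)) + 1/80)
- false-positive rate = Φ(b/SE − 1.96) + Φ(−b/SE − 1.96)

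Worked case, q = 20% and r = 0.3: λ = 0.280/0.8 = 0.350; b = 0.3 × 0.44 × 0.350 = 0.046 kg; v = 1 − 0.09 × 0.350 × (0.350 + 0.842) = 0.9625; SE = 0.44 × √(0.9625/64 + 1/80) = 0.0730; b/SE = 0.633; rate = 0.092 + 0.005 = 9.7%.

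| q | r | bias (kg) | share of 0.35 kg | false-positive rate |
|---|---|---|---|---|
| 10% | 0.2 | +0.017 | 5% | 5.7% |
| 20% | 0.3 | +0.046 | 13% | 9.7% |
| 20% | 0.5 | +0.077 | 22% | 19% |
| 30% | 0.5 | +0.109 | 31% | 32% |

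A larger trial makes the error rate worse: with 100 per arm, the second row gives 10.9%.

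**Severe-malnutrition rule alone.** As a stand-in, children below the same weight-gain cut-off are removed from both arms. With no true effect there is no bias. Under the protocol's expected means and SDs, a cut-off that removes 2%, 5% or 10% of controls removes at most 0.3% of RUTF children. The difference falls from 0.35 kg to about 0.33, 0.30 or 0.27 kg, which works against RUTF.

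**Both rules together** (5% to 20% low intake, r from 0.1 to 0.5, cut-off removing 2% to 10% of controls). The net bias is +0.001 to +0.065 kg with no true effect, and −0.078 to +0.036 kg under the expected effect.

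**The case against.** Four points can be made on the other side.

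- **Leaving withdrawn children out of the analysis is inferred.** The protocol never says so, and an analysis set may properly be left to an analysis plan. A low-intake child who attends the two-week visit can be weighed there, so the primary result is biased by the sachet rule only if that weight is then discarded. This stands, and the conclusion is conditional on it. It does not dispose of the point, because the protocol itself fixes the one-sided withdrawal and no later plan can recover weights that were never taken.
- **The size rests on two assumed quantities.** Sections 3.4 and its quantity paragraph describe the product as well accepted and liked, so few children may fall below 10 of 14 sachets. With 5% withdrawn and r = 0.1 the bias is 0.005 kg and the false-positive rate about 5.1%, which is negligible. This stands: the table is a range, not a prediction.
- **The figures are in kg, while section 4.2 defines the outcome in g/kg/day.** This is true, but the sample size is also in kg. In SD units the shift is r × λ (0.3 × 0.350 = 0.105 SD in the middle case), whatever the unit, if r is the same.
- **A reader might infer that all the withdrawal rules favour RUTF.** The protocol does not support that. Apart from the sachet rule, they apply to both arms. Severe-malnutrition withdrawal would remove mainly poorly growing controls if RUTF works. Treatment failure is judged on D2 under directly observed treatment in both arms, and no direction can be read from the text.

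**Conclusion.** The point holds for the sachet rule. It is asymmetric, acts after randomisation and answers a question other than the stated objective. It biases the comparison towards RUTF if withdrawn children are dropped and poor eaters gain less. Under the assumptions shown, the spurious gain is +0.017 to +0.109 kg (5% to 31% of the planned difference) and the false-positive rate 5.7% to about 32%. With lower withdrawal and correlation it is close to nothing.

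For the rules that act in both arms, the defect is selection on post-randomisation events and possible loss of the two-week and four-week weights. Severe-malnutrition withdrawal would dilute a real effect and distort the weight-loss outcome. The direction for treatment failure is unknown. The net direction of all rules together is therefore uncertain, and it would be wrong to conclude that the plan as a whole is tilted towards RUTF.

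**What to change.** In sections 3.2.3 and 7.4, separate stopping study RUTF, or referral for care, from leaving follow-up. State that all randomised children whose caregivers still consent are weighed at the already scheduled 14- and 28-day visits where possible, including those referred for care, and that the primary analysis is by allocated arm. Delete the 10-sachet limit as a reason for withdrawal. Keep the Annex 4 sachet counts as adherence data for a labelled secondary per-protocol analysis. Clinical care and referral stay as they are.

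The costs are modest. Obtaining weights from referred children takes some effort and may need an arrangement with the feeding programme. Care that they receive there becomes part of the as-randomised contrast. The as-randomised effect will also be somewhat smaller. If 20% eat too little and gain nothing extra (an assumption), the expected difference is 0.8 × 0.35 = 0.28 kg. With average SD √((0.44² + 0.33²)/2) = 0.389 and 100 per group, 0.28/(0.389 × √(2/100)) = 5.09, so power is Φ(5.09 − 1.96), above 99%.

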**3.2.4 Follow-up**

Compensation for returning to the clinic will be provided to encourage follow-up at day 14 and day 28, in both study groups. The value of the compensation (in kind) will be approximately equivalent to one-day labour costs as this is roughly equivalent to the travel time and time spent in the clinic.

Active follow-up will be attempted for those who do not attended their appointments.

**3.3. Sampling frame**

The nature of the intervention means that blinding of health workers and participants is not possible. In order to address observer bias, the interviews will be carried out by field staff who are not part of the normal health services staff of the study clinics.

The sample size is based on the hypothesis that, compared to a control group of children who receive routine malaria treatment without nutritional supplementation, children receiving supplementation will show significantly greater average weight gain over the study period.

The following is the basic formula for calculating required sample size in each group (assuming equal numbers sampled in each group) for the difference between two population means[[20]](#footnote-4) :

n>2 ((z 2α σ)/d)2

Where:

n=number sampled in each population

d= difference in sample means

σ =standard deviation

Z2α = standardised normal deviate exceeded by specified probability

Assumptions for sample size calculations have been based on two previous studies from the Gambia assessing the impact of infection on weight gain. The first study, carried out in 1977, demonstrated that the incidence of either malaria or diarrhoea have a significant negative effect on weight gain.6 The second study, an intervention study published in 1996, demonstrated that short-term nutritional supplementation for diarrhoea had a significant impact on weight gain.10 This study provides the parameters for the sample size calculation, while the first study provides the basis on which we extrapolate the evidence that nutritional supplementation may address post-infection lack of weight gain related to diarrhoeal disease, to a similar impact on post-malaria weight gain. The primary sample size calculation is based on demonstrating a statistically significant difference in mean weight gain/loss between the intervention and control groups at two weeks.

# Expected mean change in weight for control and intervention groups are: 10

- Control group 0.09 kg/14 days (standard deviation 0.44)

- Intervention group 0.44 kg/14 days (standard deviation 0.33)

(For all calculations, power of 80% and 5% level of significance for a two- sided test of hypothesis was used. The Z2α would be in this case1.96)

Applying the parameters on the formula given above for means of 0.09 and 0.44, and standard deviation of 0.44, results in a required sample size is 13. This is quite small because even though the standard deviation is comparatively large, the magnitude of the 2 means is very different.

However, this assumes equal variances in the two population means. Statistical software (STATA version 10.0, STATAcorp, College Station, Texas, USA, 2007), was used for the sample size calculation, which adjusts for unequal variances, and therefore gives a larger sample size of 20 per group.

Estimated sample size required per study group:[[21]](#footnote-5)

- Sample size per group: 20
- Required samples size per group (adjusted for 20% loss to follow-up): **24**

However, the difference between our study and the 1996 study is that the subject of that study was weight gain after diarrhoea, while our study will assess weight loss/gain after an episode of malaria. The 1977 study on the relationship between disease and weight loss showed that both diseases are associated with weight loss, but that for diarrhoea weight loss was more prevalent than for malaria. As the sample size above is considered the minimum, we aim to increase the sample size in order to increase the power of the study to take into account the expected higher variation in weight loss of children with malaria compared to children with diarrhoea.

The total sample size is defined by the minimum sample size (see above) and a sample size that is defined by the number of subjects that can realistically be enrolled in a day during a period of four weeks; enrolment of 10 malaria patients per day for 4 weeks (5 working days per week) gives a sample size of 100 per study group. As not all children will be eligible due to the inclusion/exclusion criteria, a sample size of 80 is thought to be a realistic target.

The number of children presenting with malaria in the clinic outweighs the number to be enrolled: in May 2007, 600 children under 5 years with P. falciparum malaria were treated in 4 weeks. Therefore sampling 1 out of 3 malaria cases would result in a sample size of approximately 100 per study group.

Therefore the proposed sample size is 100 per group.

The sample will be drawn from the group of children who come to the clinic, have been clinically reviewed and are suspected malaria cases. If the malaria rapid diagnostic test is positive, from this group **one in three** child will be selected randomly, and invited to join the study. This selection procedure is necessary as more children will be presenting with malaria then study can process in a day. After explaining the study and the consent procedure, the patient will be randomly allocated to either the control group or the intervention group. The random number function of a pocket calculator will be used for randomisation. In the first step numbers ending on 3,6 and 9 will be invited for the study, numbers ending on 1,2,4,5,7,8, will not be invited, and when a number ends no 0 a new random number will be generated. Numbers ending on an even number or a zero will be in the intervention group, numbers ending on uneven will be in the control group.

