**7.2. Staff, Training, and Supervision**

There will be 4 additional staff for 2 months to ensure adequate assessments at admission, discharge and follow-up of defaulters, for monitoring during the treatment phase and for performing the laboratory work. As the staff will not be blinded for selection of participants or for allocation of the supplement the potential exists for observer bias. This will be addressed by selecting staff- to be responsible for the interviews- who are not currently involved in health care provision within MSF clinics or having regular duties in the clinic.

Training of identified staff on the aims and procedures of the study and role of staff will take place before the study starts by the expatriate field research supervisor. Staff will be trained including practical demonstration of their specific tasks, such as interviews, weight measurements, and laboratory techniques (including the correct use of Paracheck®)

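### Allocation by an on-site pocket-calculator draw, with no record, no binding first draw and no independent list, could be steered without trace in this open trial

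*Protocol*

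**What the plan says.** Protocol section 3.3 describes two uses of a random digit. The device is fixed: "The random number function of a pocket calculator will be used for randomisation".

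- **Invitation, among children with a positive rapid test.** "In the first step numbers ending on 3,6 and 9 will be invited for the study". The other six non-zero digits mean no invitation, and a final 0 is redrawn.
- **Allocation.** "After explaining the study and the consent procedure, the patient will be randomly allocated to either the control group or the intervention group". The rule is: "Numbers ending on an even number or a zero will be in the intervention group, numbers ending on uneven will be in the control group".

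The planned split is 100 per group (synopsis and section 3.3). Section 3.3 also says that health workers and participants cannot be blinded. Section 7.2 adds: "As the staff will not be blinded for selection of participants or for allocation of the supplement the potential exists for observer bias". The remedy in both sections is to take interviewers from outside the clinics' usual staff.

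**The concern.** A calculator draw leaves nothing behind. Whoever presses the key sees the result at once and can press again, and no one could tell afterwards. Concealed allocation matters most in an open trial, because no later blinding limits the damage.

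The document itself shows why someone might prefer one arm. Section 11 describes the RUTF as a temporary benefit, and section 3.1 says that controls will not receive it at the end of the study. Only severe malnutrition is excluded (section 3.2.2), so thinner but non-severe children are randomised alongside well-nourished ones. If staff steered RUTF towards children who looked most in need, the arms would differ at baseline in something plausibly related to catch-up growth, which is the primary outcome. Neither a larger sample nor modelling reliably repairs that, and allocation cannot be redone after enrolment.

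**Working it through.** **1. Does the written rule reproduce the planned numbers?** The inputs are the digit rules and the figure of 600 malaria cases in four weeks, all from section 3.3.

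- Invitation: 0 is redrawn, so nine digits remain and three are invited. 3/9 = 1/3, which matches the stated one in three. 600 × 1/3 = 200 children, or 100 per group.
- Allocation with a fresh digit: 0, 2, 4, 6 and 8 give RUTF. 5/10 = 0.50, and 200 × 0.50 = 100 per group.

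Read as two separate draws, the rule gives the planned 1:1 split.

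**2. What can repeated pressing do?** With a fair digit and unlogged repeats, the chance of reaching a wanted arm within k presses is 1 − 0.5^k:

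| Presses | Chance of wanted arm |
| --- | --- |
| 1 | 1 − 0.5 = 50% |
| 2 | 1 − 0.25 = 75% |
| 3 | 1 − 0.125 = 87.5% |

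This is what a deliberate breach could achieve for one child. It is not a forecast of how often a breach would happen. Turning it into a bias in weight gain would need the share of children affected and how their expected growth differs from the rest, and the protocol gives neither.

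**3. Would a repeated draw be detected?** The places where a trace could be expected are:

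- Section 3.3: no operator, witness, log or list, and no statement that the first number stands.
- Annex 2 (enrolment checklist): ends with consent, inclusion and study ID, with no field for the number drawn or the arm.
- Annex 3 (intake form): no such field.
- Annex 4 (follow-up form): shows the arm only indirectly, through questions put to the RUTF group alone.
- Section 7.1 (quality control): names records, interviews, clinical procedures and the rapid test, but not randomisation.

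**4. Is a second number required in so many words?** It is not. If the invitation number were reused, only 3, 6 and 9 would remain and only 6 is even. That gives 1/3 to RUTF, about 67 against 133. The variance of the difference, with equal SDs, would change by (1/66.7 + 1/133.3)/(2/100) = 1.125.

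The effect on power is small (normal approximation, two-sided 5%):

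| Difference | SDs, RUTF/control | 100/100 | 67/133 |
| --- | --- | --- | --- |
| 0.35 kg (0.44 − 0.09, section 3.3) | 0.33/0.44 (section 3.3) | above 99.9% | above 99.9% |
| 0.15 kg (assumed, for illustration) | 0.33/0.44 | 77.9% | 77.1% |
| 0.15 kg (assumed) | 0.44/0.44 | 67.4% | 62.4% |

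So the wording gap matters little for precision. The lasting weakness is the repeatable, unrecorded draw.

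**The case against.** Several points on the other side are sound.

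- **The next assignment cannot be foreseen.** A fresh draw made after the consent procedure tells nobody the arm in advance. This stands. The weakness is that a result can be discarded, not that it can be predicted.
- **No redraw is authorised at allocation.** A reader might infer that the protocol makes redrawing routine. It does so only at invitation: "when a number ends no 0 a new random number will be generated". The allocation rule assigns every digit, including zero.
- **The operator is unknown.** A reader might infer that clinic staff allocate. The protocol names no one, and section 7.2 provides four additional study staff. What can be said is that staff are unblinded and the operator is unspecified.
- **A 1:2 allocation is not the likely meaning.** The invitation rule is called the first step, which implies another. The rule "Numbers ending on an even number or a zero will be in the intervention group" needs a new number, because a zero cannot survive the invitation step. The plan is also for 100 per group.
- **There are partial safeguards.** Severely malnourished children are referred to therapeutic feeding, which removes the strongest reason to steer. Section 3.1 expects randomisation to be acceptable and reports no problem in a similar study. Baseline nutritional status is measured, so imbalance in it would be visible. A supervisor checks adherence to the protocol. All of this lowers the risk, but none of it would reveal a discarded draw. Adjustment (section 10) covers only measured factors that are kept in the model, not an unrecorded impression of need.
- **A log is not ruled out.** That is true, but the protocol sets out the procedure and its forms in detail, and none of them provides one.

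Chance imbalance under simple randomisation is no part of the point. A split of 90:110 or worse has a probability of about 18%, but 90:110 raises the variance of the difference only by the factor (1/90 + 1/110)/(2/100) = 1.010.

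**Conclusion.** The concern holds as a weakness in the allocation procedure that the protocol itself fixes. In an open trial with staff acknowledged to be unblinded, the arm is set by an on-site draw that can be repeated without trace. The outside interviewers protect assessment, not allocation. One unseen redraw moves the chance of a wanted arm from 50% to 75%, assuming a fair digit and someone willing to discard a result.

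The documents do not support the inference that steering is expected, that the arm is known before consent, or that allocation is really 1:2. The size of any bias cannot be derived from them. The unstated second draw is a lesser gap that one sentence would close. Because random assignment is the basis for attributing weight gain to RUTF, and the remedy is cheap, the change should be made before enrolment.

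**What to change.** Keep the one-in-three invitation draw. Replace the allocation draw with a 1:1 list generated off site and held in sequentially numbered, sealed, opaque envelopes. Open and log the next envelope only after eligibility, consent and study ID are recorded in Annex 2. The cost is preparing and logging about 200 envelopes, plus a paragraph of protocol text.

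If the calculator is kept, section 3.3 should at minimum state that a separate number is drawn after consent, that the first draw is binding, and that every number and arm is recorded on the enrolment form. Annex 2 would need fields for both. This closes the wording gap and leaves a record, but it still depends on the operator entering the first number, so the envelopes are the better choice.
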